**Patients**

Patients with primary liver cancer who is scheduled for open hepatectomy with ERAS programs (**Table 1**) will be evaluated for eligibility. Inclusion criteria are as follows: age between 18 and 65 years; body mass index of 18.5-28 kg/m^2^; number of tumor less than 3; tumor’s maximum diameter or sum of diameters smaller than 10 cm; class A or B of Child-Pugh liver function; tumor’s clinical stage as I or II; the remaining liver volume/standard liver volume ratio of >40%; no difficulty of intubation or inserting an LMA; American Society of Anesthesiologist physical status classification between I and III. Exclusion criteria are as follows: presence of comorbidities such as diabetes, pathological cardiopulmonary disease and renal insufficiency; a New York Heart Association class of heart function of III or greater; intrahepatic vascular invasion or extrahepatic metastasis of tumor seen by computerized tomography (CT) or magnetic resonance imaging (MRI); having received chemotherapy or radiotherapy before surgery; having undergone abdominal surgery; infection of the site of TAP block; allergy to any study medication; a history of alcohol or drug abuse; difficulty of communication with family or hospital staff. After randomization, patients who experience a failure of TAP block or LMA ventilation, suffer systemic poisoning from local anesthetic, are found to have extensive metastasis of tumor after laparotomy, lose blood over 1000 ml during surgery, undergo a long operating time of over 6 hours (hr), need to be transferred into intensive care unit (ICU) after surgery, or refuse to go on participating in this trial will br excluded from the analysis.

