**Study end-points**

The primary end-point of the study is postoperative time of readiness for hospital discharge. The discharge criteria include: pain score less than 4, solid diet without infusion, normal bowel movement, well-healed wound, normal organ function, normal count of white blood cell (WBC), no fever, life independence.

The secondary end-points are postoperative analgesic requirement within 48 hr, time to first flatus and overall medical cost. Blood glucose and lactate will be tested before anesthesia (t0), at surgical exploration (t1), at the conclusion of surgery (t2) and at departure from the post-anesthesia care unit (PACU) (t3). Dosages of anesthetics and vasoactive drugs, surgery duration, anesthesia duration, hepatectomy duration, duration of hepatic blood flow occlusion, bleeding volume, infusion volume and urine volume are recorded.

The postoperative pain intensity of the surgical site is assessed with the numerical rating scale (NRS), in which 0 represented no pain and 10 represented the most severe pain. Postoperative variables such as time to removing ETT or LMA, duration of PACU stay, time to first mobilization off the bed, incidence of nausea/vomiting within 48 hr and complications are also recorded and compared. The 40-item quality of recovery (QoR-40) survey is performed before surgery, at 1 and 3 days after surgery, and on the day of discharge, referred to other studies^[12, 13]^ and described as **the following figure**.

| **QoR-40 Questionnaire** | | | | | | | | |
| --- | --- | --- | --- | --- | --- | --- | --- | --- |
| Date:____/____/____ | Preoperative:_______ | | | Postoperative:______ | | | Study #:______ | |
| **PART A** | | | | | | | | |
| ***How have you been feeling in the last 24 hours?*** | | | | | | | | |
| (1 to 5, where: 1 = none of the time [poor], 2 = sometimes, 3 = often, 4 = most of the time, 5 = all of the time [excellent]) | | | | | | | | |
|  | | none of  the time | sometimes | | often | most of  the time | | all of the time |
| 1.Able to breathe easy | | 1 | 2 | | 3 | 4 | | 5 |
| 2.Being able to enjoy food | | 1 | 2 | | 3 | 4 | | 5 |
| 3.Have a good sleep | | 1 | 2 | | 3 | 4 | | 5 |
| 4.Feeling rested | | 1 | 2 | | 3 | 4 | | 5 |
| 5.Feeling comfortable | | 1 | 2 | | 3 | 4 | | 5 |
| 6.Having a general feeling  of well-being | | 1 | 2 | | 3 | 4 | | 5 |
| 7.Feeling in control | | 1 | 2 | | 3 | 4 | | 5 |
| 8.Able to write | | 1 | 2 | | 3 | 4 | | 5 |
| 9.Have normal speech | | 1 | 2 | | 3 | 4 | | 5 |

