**Statistical analysis and sample size**

Statistical analyses will be performed with SPSS software version 19.0 (IBM Corporation, Armonk, NY, USA). Continuous variables are expressed as mean ± standard deviation and tested if they are normally distributed. Variables with normal distribution are compared between groups using a 2-sample Student’s *t*-test. Data without normal distribution are analyzed using non-parametric test. Blood glucose, lactate, the NRS pain score and the QoR-40 score will be compared between groups using repeated-measures analysis of variance (ANOVA). Categorical data is expressed as ratio or frequency and analyzed using Chi-square test or Fisher’s exact test. Two-tailed *P*<0.05 indicates statistical significance.

Based on our preliminary experiment consisting of 24 patients, the sample size for this trial is calculated using SAS software version 9.4 (SAS Institute Inc., Iowa City, IA, USA). The postoperative time of readiness for hospital discharge in the control group was (9 ± 2.5) days, while that of the TAP+LMA group was (7.5 ± 2.0) days. Accordingly, 42 patients are required per group to achieve 85% statistical power (1-β) at a significance level (α) of 0.05. To account for a 15% drop-out rate, we will enrolled 48 patients per group finally.

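### The primary comparison is not fixed in advance: a normality check on the trial's own data chooses between a t-test and an unnamed rank test, and neither uses the surgeon strata

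*Protocol*

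**What the plan says.** Protocol, Study end-points: "The primary end-point of the study is postoperative time of readiness for hospital discharge". Readiness means meeting a list of criteria that covers pain, diet and bowel movement and ends with "well-healed wound, normal organ function, normal count of white blood cell (WBC), no fever, life independence".

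Protocol, Statistical analysis and sample size: "Continuous variables are expressed as mean ± standard deviation and tested if they are normally distributed". Then: "Variables with normal distribution are compared between groups using a 2-sample Student’s *t*-test". Otherwise: "Data without normal distribution are analyzed using non-parametric test". The section does not name the normality test, say whether it is applied per arm or pooled, or name the non-parametric test. It gives the primary end-point no rule of its own. The sample size rests on the mean and SD of that end-point in a 24-patient preliminary experiment: 9 ± 2.5 days (control) and 7.5 ± 2.0 days (TAP+LMA).

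Protocol, Randomization and blinding: allocation is stratified by surgeon. The analysis text does not mention the strata.

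Protocol, Patients: eligibility includes "class A or B of Child-Pugh liver function". A separate list of post-randomization exclusions ends with patients who are "transferred into intensive care unit (ICU) after surgery, or refuse to go on participating in this trial will br excluded from the analysis".

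**The concern.** A primary analysis should state one comparison before the data are seen. Here the quantity compared (a difference in means or a shift in ranks) depends on a preliminary test of the same data, and the details of that test are open. Two analysts following the text could report different primary tests. Leaving out the surgeon strata also sets the analysis apart from the randomization and gives up precision if surgeons differ in their patients' recovery times.

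The end-point adds a second difficulty. It is a time to meeting criteria, while both permitted tests need an observed number for each patient. A patient who dies or leaves before readiness has no such number, and those are among the worst outcomes.

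**Working it through.** **1. The plan's own figure.** Inputs (Statistical analysis and sample size): means 9 and 7.5 days, SDs 2.5 and 2.0, two-sided α 0.05, power 85%.

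- Difference = 9 − 7.5 = 1.5 days.
- Pooled variance = (2.5² + 2.0²)/2 = (6.25 + 4.00)/2 = 5.125, so SD = 2.264.
- Normal approximation: n = 2 × 5.125 × (1.960 + 1.036)² / 1.5² = 40.9, so 41 per group.
- Exact (noncentral t) power: 84.2% at 41 and 85.1% at 42.

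The stated 42 per group reproduces as a t-test calculation. The design thus assumes a comparison of means with an observed time for every analysed patient.

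**2. The two-stage rule.** Assumptions, because the protocol gives none: times recorded in whole days; Shapiro-Wilk at 0.05 in each arm, with failure in either arm triggering the switch; Mann-Whitney as the rank test; 42 per arm. Means and SDs are the protocol's; under no effect both arms have 9 ± 2.5. Runs: 8,000 per row.

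| Distribution | Scenario | t-test significant | Rank test significant | Two-stage rule significant | Trials that switch |
|---|---|---|---|---|---|
| Rounded normal | No effect | 4.8% | 4.7% | 5.0% | 31% |
| Rounded normal | Planned effect | 84.6% | 82.9% | 83.8% | 42% |
| Rounded lognormal | No effect | 4.9% | 4.8% | 4.9% | 85% |
| Rounded lognormal | Planned effect | 85.6% | 83.9% | 84.2% | 90% |

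For gamma data under the planned effect about 72% of trials switch. Further simulations on the same set-up show:

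- Always taking the smaller of the two p-values gives a type I error of about 6%.
- The t-test and the rank test give different significance verdicts in about 5% of trials under the planned effect.

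**3. Price of fixing a rank test.** From the rounded-normal row: 84.6 − 82.9 = 1.7 points. Across the simulations run, the loss is about 1-3 points. Stratifying by surgeon gains power if surgeons differ enough in their patients' recovery times; the protocol gives no figure for that.

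**4. Patients without a readiness time.** The documents give no rate, so the rates below are assumed. Lognormal times, 42 per arm, planned effect, 4,000 runs.

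| Never ready (control / TAP+LMA) | Power if dropped (t-test) | Power if ranked worst (unstratified rank test) |
|---|---|---|
| 2% / 2% | 86% | 81% |
| 5% / 5% | 84% | 75% |
| 10% / 10% | 82% | 66% |
| 0% / 10% | 84% | 44% |

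The last row matters most. If such patients occurred only in the experimental arm, dropping them would leave the result almost untouched, while keeping them would change it greatly. An analysis of all 48 randomised per arm would have somewhat more power than these figures for 42.

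**The case against.** **The harm from the pre-test is small.** This stands as far as error rates go. The text is a conditional rule and not a free choice of p-value. Type I error stays near 5%, and even abusing the rule adds only about one point. A reader might infer that the switch inflates false positives; the simulations do not support that. A switching rate of 85-90% for skewed data also shows the check responding to the distribution, not to chance alone. What remains is that the compared quantity and the test are open until the data are in.

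**An unseen statistical analysis plan may give the missing detail.** It may, and a missing rule for deaths or early leavers is therefore not a fault in itself. But the protocol does more than stay silent: it states a data-driven choice of test, and that sentence stands until it is changed.

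**Child-Pugh B patients.** A reader might infer that they can never reach "normal organ function, normal count of white blood cell (WBC), no fever, life independence" and so fall out of the primary analysis. The documents do not support this. The criterion has no threshold, blinded surgeons apply it, and neither the share of Child-Pugh B patients nor any never-ready rate is given. The preliminary experiment reports times by group and mentions no patient without one. The two passages sit badly together and need reconciling; nothing further follows.

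**ICU transfers and refusals.** It is tempting to blame the t-test for losing them. They are removed by the explicit exclusion rule under Patients, whichever test is used. Changing the test does not cure that rule.

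**Conclusion.** The point holds as a defect in a stated rule. The protocol leaves the primary comparison to a normality check on the trial's data, leaves the alternative test unnamed, and uses no surgeon strata. The size is modest: type I error about 5% (at most about 6%), a switch in roughly 30-90% of trials, and a different verdict from the two tests in about 5% of trials under the planned effect. These figures assume whole-day data and Shapiro-Wilk in either arm. That the rule governs the primary end-point follows from its covering all continuous variables and from the t-test sample size, since the section does not say so expressly.

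The handling of patients who never become ready could matter more, but its size rests wholly on assumed rates. It is a reason to settle the handling together with the test, not evidence of bias in this trial.

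**What to change.** - Drop the normality pre-test for the primary end-point and name one surgeon-stratified test before analysis. One suitable choice is the van Elteren test with a Hodges-Lehmann difference and confidence interval, and the mean difference as supportive. The cost is about 1-3 points of power if data are normal and surgeons do not differ, with a gain if they differ enough.
- In the same analysis, keep patients who die or leave before readiness as unfavourable outcomes. Either worst ranks or a stratified time-to-event analysis that counts them as never ready would serve; the essential step is to choose one.
- Restate power if such patients are expected. At an assumed 5% per arm, worst-rank power with 42 per arm is about 75%, against the planned 85%, so the 1-3 point cost would no longer be the whole cost.
- Reconcile the organ-function discharge criterion (Study end-points) with Child-Pugh B eligibility (Patients). Which wording to change is for the sponsor.
- Treat the post-randomization exclusions under Patients as a separate matter.

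All of this is a change of wording and analysis, with no new visits or data. Only the restated power could affect the sample size.

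### Glucose, lactate and QoR-40 go to repeated-measures ANOVA with no baseline covariate although their first occasion precedes treatment; a four-occasion group main effect would estimate only 0.75 of the mean post-treatment effect

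*Protocol*

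**What the plan says.** The protocol's section on statistical analysis and sample size fixes one method for four measures: "Blood glucose, lactate, the NRS pain score and the QoR-40 score will be compared between groups using repeated-measures analysis of variance (ANOVA". It adds "Two-tailed *P*<0.05 indicates statistical significance". It names no covariate for these measures, does not say whether the pre-treatment value enters as one of the repeated occasions, and does not say whether the group term or the group-by-time term is the test.

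The section on study end-points gives the occasions. "Blood glucose and lactate will be tested before anesthesia (t0), at surgical exploration (t1), at the conclusion of surgery (t2) and" on leaving the recovery unit (t3). The QoR-40 "survey is performed before surgery, at 1 and 3 days after surgery, and on the day of discharge". Each of these three measures therefore has four occasions, the first of them before treatment. The sections on interventions and on anesthesia place the airway device and the TAP block after induction, so t0 and the preoperative QoR-40 precede both. No preoperative NRS assessment is stated.

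**The concern.** At a pre-treatment occasion, randomisation makes the expected group difference zero. An ANOVA group effect taken over all four occasions averages that zero with three post-treatment differences. The same analysis also leaves unused the information in each patient's own baseline, which could remove part of the between-patient variance. A real effect on recovery quality or on the metabolic stress response could then be reported as no difference, although the data that would show it are already being collected. The QoR-40 matters most here: it is the trial's patient-reported measure of recovery, and the flow diagram lists quality of recovery among the study end-points.

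**Working it through.** **The plan's own figure.** The only sample-size calculation concerns the primary end-point: "in the control group was (9 ± 2.5) days" and the "TAP+LMA group was (7.5 ± 2.0) days". The pooled SD is √((2.5² + 2.0²)/2) = 2.264 and the difference is 1.5 days. With the noncentral t and two-sided α = 0.05, 41 per group gives 84.2% power and 42 gives 85.1%. The stated figure, "42 patients are required per group to achieve 85% statistical power (1-β) at a significance level (α) of 0.05", reproduces. It says nothing about glucose, lactate or QoR-40, for which the protocol gives no effect size, SD or correlation.

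**Inputs.** From the protocol: n = 42 per group, α = 0.05 two-sided, four occasions of which one is pre-treatment. Assumed: SD 1 at every occasion, compound symmetry with correlation r of 0.3, 0.5 or 0.7, and a group effect of 0 at baseline and d1, d2, d3 afterwards.

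**Size of the dilution.** The four-occasion group effect is (0 + d1 + d2 + d3)/4. The mean post-treatment effect is (d1 + d2 + d3)/3. Their ratio is 3/4, whatever the time pattern or correlation.

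**Power formulas.** Write d for the mean post-treatment effect.

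- Four-occasion group main effect: effect 0.75d, variance v = (1 + 3r)/4, t with 82 df.
- Post-treatment mean without covariate: effect d, v = (1 + 2r)/3, 82 df.
- ANCOVA of the post-treatment mean on baseline: effect d, v = (1 + 2r)/3 − r², 81 df.
- For these three, the noncentrality is effect/√(2v/n).
- Group-by-time: F with 3 and 246 df, noncentrality λ = (n/2) × S/(1 − r), where S is the sum of squared deviations of (0, d1, d2, d3) from their mean. For a sustained effect S = 0.75d².

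**Worked case: sustained 0.4 SD, r = 0.5.**

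- Main effect: v = 0.625, so 0.30/√(1.25/42) = 1.74, power 41%.
- ANCOVA: v = 0.6667 − 0.25 = 0.4167, so 0.40/√(0.8333/42) = 2.84, power 80%.
- Group-by-time: λ = 21 × 0.12/0.5 = 5.04, power 44%.

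| r | Group main effect, 4 occasions | Group-by-time | ANCOVA |
|---|---|---|---|
| 0.3 | 51% | 32% | 78% |
| 0.5 | 41% | 44% | 80% |
| 0.7 | 34% | 67% | 90% |

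**Where the loss comes from.** At r = 0.5, dropping the covariate but keeping only post-treatment occasions takes power from 80% to 60%. Averaging the baseline in takes it on to 41%. Both steps matter.

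**Efficiency of the main effect relative to ANCOVA**, 0.75² × ((1 + 2r)/3 − r²)/((1 + 3r)/4): 0.75 at r = 0, 0.53 at 0.3, 0.38 at 0.5, 0.23 at 0.7.

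**Other effect patterns.** The ranking of group-by-time against ANCOVA depends on the pattern.

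| Pattern (SD) | r | Group-by-time | ANCOVA of post-treatment mean |
|---|---|---|---|
| Fading 0.6, 0.3, 0 | 0.3 / 0.5 / 0.7 | 61 / 77 / 95% | 53 / 56 / 68% |
| Late 0, 0.6, 0.6 | 0.3 / 0.5 / 0.7 | 79 / 92 / 99% | 78 / 80 / 90% |

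The four-occasion main effect stays below ANCOVA in both. At r = 0.5 it has 25% power for the fading effect (0.225/√(1.25/42) = 1.30). For the late effect it has 41%, because the post-treatment mean is again 0.4.

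**The case against.** Four objections deserve an answer.

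**The protocol does not name the tested term.** A reader might infer that the baseline certainly enters as an outcome occasion and that the reported effect is therefore cut by a quarter. The document does not say so. Listing four occasions and comparing groups makes that a natural reading, but group-by-time is also possible and carries no such dilution. This objection stands, and the point is conditional because of it.

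**Covariates and contrasts are commonly left to the SAP.** True, and the absence of such detail alone would be no finding. Here, however, the protocol does name a method for these measures, and that method, taken as written, does not use the baseline well. The point is a better choice in place of a stated one.

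**A sustained effect is the pattern kindest to ANCOVA of the mean.** This stands. The last QoR-40 is on the day of discharge, and the discharge criteria require a low pain score, solid diet and independence, so the groups may well converge by then. Under fading or late effects, group-by-time can outperform ANCOVA of the post-baseline mean. It would be wrong to conclude that every form of repeated-measures ANOVA loses much power here. The objection does not rescue the four-occasion main effect.

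**The consequence is limited.** Also true. These measures are neither the primary end-point nor in the sentence that names the secondary end-points. Including the baseline leaves type I error unaffected.

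**Conclusion.** The point holds in conditional form. If the test is the group main effect over all four occasions, the 0.75 factor is exact and needs no assumption beyond randomisation and a pre-treatment first occasion. The power loss is large, but its size rests on assumptions the protocol does not supply: for a sustained 0.4 SD effect with 42 per group and compound symmetry, a shortfall against ANCOVA of about 27, 39 and 56 percentage points at correlations of 0.3, 0.5 and 0.7. If the test is group-by-time, the effect is not diluted, and whether power falls short of ANCOVA depends on how the effect evolves.

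The documents do not support the stronger inference that the effect is diluted whichever term is tested. Nor do they support any inference that the primary analysis, the sample size or the validity of the tests is compromised. This is an improvement in efficiency and clarity for supportive outcomes, and it is worth making because it is nearly free.

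**What to change.** For glucose, lactate and QoR-40, replace the present sentence with one to this effect: the post-baseline occasions are the response in a repeated-measures model with group, occasion, group-by-occasion and the patient's own pre-treatment value (t0, or the preoperative QoR-40) as covariate. The contrast tested is the baseline-adjusted mean group difference over the post-baseline occasions, reported with a 95% CI. Differences at each occasion are given as well where the effect may change over time, as with the QoR-40 towards discharge. The NRS pain score needs no change on this account.

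The cost is an edit of a sentence or two, made before group outcomes are examined. It needs no new data, patients or software.

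### Minor arithmetic slip: 48 per group does not fully cover a 15% drop-out; it keeps the required 42 evaluable per group only up to 12.5% loss

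*Protocol*

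**What the plan says.** All of the relevant text is in the Protocol, section 'Statistical analysis and sample size'.

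- Planning values come from a preliminary experiment in 24 patients: "The postoperative time of readiness for hospital discharge in the control group was (9 ± 2.5) days". For the experimental arm the corresponding mean is 7.5 days, with an SD of 2.0.
- Evaluable number: "42 patients are required per group to achieve 85% statistical power". The type I error rate for this calculation is 0.05.
- Enrolment: "To account for a 15% drop-out rate, we will enrolled 48 patients per group finally".
- Test and sidedness: "Variables with normal distribution are compared between groups using a 2-sample Student’s *t*-test", with a non-parametric test otherwise, and "Two-tailed *P*<0.05 indicates statistical significance".

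The section does not say how the drop-out allowance was applied, and no other part of the Protocol does so or corrects the figure.

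**The concern.** A drop-out allowance has one job: if the assumed fraction is lost, the number left should still be the number required. Taking 15% off 48 gives less than 42, so the sentence does not deliver what it says.

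The allowance has real work to do in this trial. The 'Patients' section removes randomised patients from the analysis for several reasons, among them failure of the block or the laryngeal mask, heavy blood loss, a long operation, transfer to intensive care and refusal to continue. Each such case reduces the analysed sample directly. A reader who relies on the stated 15% would believe that 42 per group survive at that rate. The Protocol gives no expected frequencies for these events, so nothing can be said here about what the actual loss will be. What is at stake is the accuracy of a stated planning property.

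**Working it through.** **Inputs**, all from the sample-size section: means 9 and 7.5 days (difference 1.5); SDs 2.5 and 2.0; two-sided α = 0.05; equal groups; power 85%; required n = 42 per group; drop-out 15%; enrolled n = 48 per group.

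**Step 1. Reproduce the 42.**
- Pooled SD = √((2.5² + 2.0²)/2) = √5.125 = 2.264.
- Standard error of the difference with n per group = √(10.25/n).
- Noncentrality = 1.5/√(10.25/n), with 2n − 2 degrees of freedom. Power is the probability that a noncentral t variable exceeds the two-sided 5% critical value in either direction.
- n = 42: noncentrality 1.5/0.494 = 3.036, power 85.1%.
- n = 41: noncentrality 1.5/0.500 = 3.000, power 84.2%.

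So 42 is the smallest number per group that reaches 85% with the t-test, and the Protocol's figure reproduces exactly.

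**Step 2. Enrolment needed for a 15% loss.** If a fraction d of those enrolled is lost, N × (1 − d) must be at least 42.
- N = 42/(1 − 0.15) = 42/0.85 = 49.4, so 50 per group (100 in total).
- Check: 50 × 0.85 = 42.5, enough; 49 × 0.85 = 41.65, not enough.
- Stated: 48 per group (96 in total), which is 2 per group short.

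**Step 3. Where 48 may come from.** 42 × 1.15 = 48.3, which rounds down to 48. This adds 15% of the evaluable number instead of allowing for 15% of the enrolled number. It is an inference from the match.

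**Step 4. What 48 per group delivers.**
- At 15% loss: 48 × 0.85 = 40.8 per group. In whole patients, losing 7 of 48 (14.6%) leaves 41, with power 84.2%. Interpolating to 40.8 gives about 84.0%.
- Largest loss that keeps 42: 1 − 42/48 = 6/48 = 12.5%.
- With no loss: power 89.5%.

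| Enrolled per group | Loss | Evaluable per group | Power (t-test) |
| --- | --- | --- | --- |
| 48 | none | 48 | 89.5% |
| 48 | 12.5% (6 of 48) | 42 | 85.1% |
| 48 | 15% | 40.8, about 41 | about 84% |
| 50 | 15% | 42.5 | at least 85.1% |

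**The case against.** The best case for leaving the sentence alone is that the discrepancy is too small to matter.

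- **Size.** One evaluable patient per group and one point of power are far below the uncertainty in the planning values, which rest on 24 patients. The 15% is itself a planning figure with no derivation given. This stands, and it is why the point is minor.
- **Choice of test.** The Protocol allows a non-parametric test if the data are not normal. As an illustration, with a relative efficiency of 0.955 (the value for a rank test under normality), power at 42 per group is 83.4%, a larger change than the drop-out slip causes. This also stands as a matter of scale, but it does not make 48 × 0.85 equal 42.
- **Normal approximation.** By that method 41 per group already give 85.1%, so 48 enrolled would nearly suffice at 15% loss. But the Protocol states 42 as its requirement. That is the t-test answer, whereas the normal approximation would have given 41. On the Protocol's own basis the allowance is short.

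Two stronger readings are tempting and are not supported. A reader might infer that the stated power and the stated drop-out rate contradict each other so badly that the sample size is unsound. The two miss each other by about one percentage point, so that is too strong. A reader might also round 40.8 down to 40 and quote a larger loss of power. Having 40 left means losing 8 of 48, or 16.7%, which is more than the Protocol assumes.

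Separately, the flow diagram shows n=48 at randomisation, before the split into arms, while the sample-size text gives 48 per group. That needs reconciling but is a different matter; the working here uses 48 per group.

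**Conclusion.** The point holds as a minor arithmetic correction. Retaining 42 evaluable per group at 15% loss takes 50 enrolled per group. The planned 48 leaves about 41 and about 84% power, and supports 85% only for losses up to 12.5%.

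This rests on the Protocol's own planning values, a two-sided two-sample t-test at 0.05, equal groups, and the usual reading of a drop-out rate as a fraction of those enrolled. The validity of the comparison is not affected. If losses stay at or below 6 per group, the stated power is met in full on these assumptions.

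**What to change.** Keep 48 per group and restate the sentence in one of two ways:

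- 48 per group allows for 12.5% drop-out with 85% power; or
- with 48 per group, 15% drop-out leaves about 41 per group and about 84% power.

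Either is numerically correct, and one is enough. The cost is one sentence and a slightly less favourable stated figure, with no change to recruitment or analysis. Raising enrolment to 50 per group would let both stated figures stand, at a cost of four more patients in total (100 − 96), but a gain of about one point of power does not call for it.
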